**Figure 1 figure1:**
[figure not shown]
Study procedure flowchart. CONT: control group; EXPE: experimental group.

### Experimental Intervention: Poppins Clinical

As aforementioned, we have already examined the impact of the first version of the digital medical device Poppins Clinical on the reading abilities of children with SLD. This version consisted of musical training in the form of a serious game [26]. Based on the new recommendation from the Collège Français d’Orthophonie [14], a new version of Poppins Clinical has been developed that combines the initial musical training program with a written language training program.

Poppins Clinical is now an app available on tablets and smartphones (iOS [Apple Inc] and Android), where children are led to carry out different activities divided into two categories: language activities and musical activities. Depending on the child’s performance, the difficulty of the proposed activities is adapted. Poppins Clinical contains several short activities, allowing for a variety of activities within a single session. Each activity lasts an average of 1.40 minutes, ensuring that it does not demand too much sustained attention from the child [33,34]. This structure of short activities ensures a fluid, coherent, and continuous experience for the user. To offer an experience suitable for as many children as possible (aged 7-11 years, both gamers and nongamers, with a wide range of tastes), the visual and narrative aesthetics of Poppins Clinical align with mainstream video game standards such as Rayman (Ubisoft) and Mario games (Nintendo), which are designed for all audiences.

#### Musical Activities

The musical activities consist of rhythmic tasks described in a previous paper [25]. In summary, all these tasks were designed to work on rhythm, as rhythm appears to be directly related to reading skills, whereas melody is not [35]. However, children with SLD showed deficits in rhythm processing [8,9]. Each task also requires the mobilization of other skills such as attention, inhibition, working memory, and motor skills, which are often impaired in children with dyslexia [36].

#### Written Language Section

The written language section combines exercises to enhance phonological awareness, reading speed, and writing accuracy (Figure 2). All exercises are proposed to associate phoneme and grapheme as recommended by the College Français d’Orthophonie [14]. Words presented in the game were chosen from the Manulex database, considering their frequency, length, and orthographic difficulty. Syntactic difficulties and vocabulary frequencies were also considered in the selection of sentences and texts presented in the game.

**Figure 2 figure2:**
[figure not shown]
Screenshots of written language tasks from Poppins Clinical.

Four types of exercises have been developed to work on different skills used to access written language:

Underlying processes: In Poppins Clinical, various activities are based on the ability to identify the sounds contained in a word (phoneme or syllable), thus calling on phonological and meta-phonological skills. These include activities to classify words according to the sounds that make them up. However, the activities (language and music) are carried out in various forms and require interaction with the digital tool in several ways, calling on visual attention skills, executive functions, and praxis.Graphophonology: Various activities are based on matching graphic representations with their corresponding sounds (syllables and words). The aim is to teach the player to link a graphic form to a phonological representation, in reading activities such as categorizing written words.Orthographic skills: Transcription activities are based on the ability to write words by working on lexical spelling (eg, knowledge of spelling irregularities), grammatical spelling (eg, differentiation of “et” or “est”), inflectional morphology (eg, plural marks), and derivational morphology (eg, recognizing prefix-radical-suffix structures). Activities such as word completion are proposed here.Semantics: Semantics activities are based on understanding written language. This involves knowing the vocabulary, understanding syntactic structures (eg, subordinate clauses) and textual structures (eg, organization of ideas in a text), and making inferences. This involves activities such as carrying out written instructions or putting a story in chronological order.

### Outcomes

The primary outcome of this study is reading accuracy, which will be measured by the number of correctly read words using the EVALEO (Ortho Edition) [37] 2-minute word reading test (EVAL2M). Noninferiority will be evaluated 12 weeks after the start of training with Poppins Clinical for the experimental group or 12 weeks after the baseline evaluation for the control group.

Safety will be assessed by monitoring adverse events reported by patients during the 12-week study duration.

Seven secondary outcomes will also be investigated. Noninferiority in reading speed, measured by the number of words read using the EVAL2M [37], will also be evaluated. In addition, noninferiority in word reading skills (speed and accuracy) and meta-phonological skills will be assessed using respectively the Alouette-R [38] text reading test and the BALE Phoneme Suppression Test [39].

The impact of Poppins Clinical on parents’ stress levels and quality of life will be measured using the Parenting Stress Index-Short Form (PSI-SF) and the EQ-5D-5L [40] quality of life questionnaire. Text comprehension will also be assessed through the computerized BMT-i test battery [41], evaluating correct answers to comprehension questions, as well as reading precision and speed. A cost evaluation will be conducted by administering a questionnaire to parents to evaluate the health and economic value of Poppins Clinical. The objective is to determine in each group the direct and indirect health care costs, including, treatment costs (eg, number of appointments and costs of each session) and work-related costs (eg, the number of days off used for health purposes).

A total of 5 exploratory end points will be investigated. The effect of Poppins Clinical on visual attention span will be assessed with the EVALEO test, using correct answer scores. The patient’s quality of life and reading and writing difficulties will be evaluated using the PedsQL 4.0 CORE [42] young child report and a self-assessment grid for reading and writing difficulties [43]. The perceptions of parents and speech therapists regarding the study’s impact on therapy will be captured via an adapted questionnaire. Finally, predictive factors of training effectiveness with Poppins Clinical will be explored to improve the individualization of the program and the use of the device through connection data.

All the outcomes are described in Table 1.

All outcomes will be evaluated 12 weeks after the start of training for the experimental group or 12 weeks after the baseline evaluation for the control group. Participants of the experimental group will have up to 14 calendar days to start training with Poppins Clinical once the baseline evaluation is completed. The results will be entered into an electronic case report form (eCRF) hosted on the web by the CRO, which will be responsible for data monitoring and treatment.

**Table 1 table1:** Measured outcomes investigated in the protocol.

Outcome	Measure
Primary outcome	Reading accuracy is measured by the number of correctly read words (EVAL2M)
Safety secondary outcome	Number of adverse events reported during the study
Secondary outcome 1	Reading speed is measured by the number of read words (EVAL2M)
Secondary outcome 2	Word reading accuracy and speed (Alouette-R)
Secondary outcome 3	Cost evaluation
Secondary outcome 4	Phoneme suppression skills (BALE)
Secondary outcome 5	Parental stress levels measured using the Parenting Stress Index Short Form
Secondary outcome 6	Parent’s quality of life measured using the EQ-5D-5L
Secondary outcome 7	Reading precision, speed, and comprehension (BMT-i)
Exploratory outcome 1	Visual attention span (EVALEO)
Exploratory outcome 2	Child’s quality of life (PedsQL 4.0 CORE)
Exploratory outcome 3	Child’s perception of reading and writing difficulties [43]
Exploratory outcome 4	Perception of parents and speech therapists on the impact of the protocol on the child (custom questionnaire)
Exploratory outcome 5	Evaluation of predictive factors of training effectiveness

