### Study Procedure

First, participants will be informed about the study either by their therapists or via web-based social media platforms. Two clinical sites in Paris and Poitiers, France, will be in charge of the screening and recruitment. Potentially eligible children and their legal representatives will receive study information during an informational visit. If interested, legal representatives will be asked to sign the informed consent form. Speech and reading therapists working with the participants will also be officially informed about the study, and their consent will be collected. The study investigator will then verify whether the participant meets the study criteria and determine their eligibility during an inclusion visit, which can be conducted either on-site or via videoconference. During this visit, verbal assent will also be obtained from the child. Following this, a baseline evaluation (T1) will be conducted by a speech therapist from the clinical site via videoconference, and questionnaires will be provided to both the patients and their legal guardians. These assessments will be performed under the same conditions as renewal evaluations, using standardized tests that have been adapted for videoconference administration.

Patients will then be randomized into one of two groups: the experimental arm or the control arm. Randomization will be carried out by the Contract Research Organization (CRO) using blocks of size six to maintain a 1:1 ratio, with stratification based on the participant’s schooling level.

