### Statistical Justification of the Sample Size

The sample size determination was based on the primary end point, which is to demonstrate the noninferiority of a follow-up with reading therapy every 2 weeks, in addition to the use of the digital medical device (Poppins Clinical), compared with a follow-up with reading therapy every week, on the evolution of reading accuracy over 12 weeks. The null (H0) and alternative (H1) hypotheses for noninferiority trials may take the following form:

H0: experimental (EXPE) is inferior in terms of the mean response, μEXPE–μCONT≤−ΔNI.H1: experimental is noninferior in terms of the mean response, μEXPE−μCONT>−ΔNI.

Where μEXPE is the mean of the outcome in the experimental arm, and μCONT is the mean of the outcome in the control arm. The noninferiority limit, –ΔNI, is defined as the threshold at which the mean difference between the experimental arm and the control arm becomes clinically unacceptable.

The noninferiority margin was determined through a formal expert committee meeting, combining independent experts and investigators. The committee was structured to ensure both independence and relevant expertise. Two independent experts were selected for their complementary expertise: a neuropediatrician who pioneered diagnostic recommendations for learning disorders in France, and a speech therapist who codeveloped the standardized assessment tool used as the primary outcome in this study (EVALEO 6-15). The two investigators of the study, both professors in child psychiatry with extensive research experience in neurodevelopmental disorders, provided their methodological expertise. A fifth expert, a neuropsychologist with experience in written language rehabilitation guidelines and as a reviewer of good practice recommendations, was included as a scientific advisor. All experts were active clinicians and researchers in learning disabilities.

The committee’s decision was informed by empirical data from the previous randomized controlled trial (ML-01), showing a natural progression of 7.7 (SD 12.9) correctly read words over 8 weeks in the placebo group [26]. Based on these data and their collective clinical experience, they established that a difference of 5 words or fewer between groups would represent a clinically acceptable margin of noninferiority. This threshold was unanimously approved by the full committee after a structured discussion of potential age-related variations in reading progression.

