The SD of the outcome in each group was estimated at 12.7 words from the ML-01 study [26]. The maximum acceptable inferiority for experimental versus control on the primary outcome is therefore expected to be a standardized difference (Cohen *d*=0.39), which corresponds to a label between small or medium, depending on the guidelines (R effect size package) [44].

Considering a one-sided significance level of 2.5% and a power of 90%, it is necessary to include 137 participants per group (G*Power 3.1). Assuming a 10% drop-out rate, the final estimate is 306 participants in total (or 153 participants per arm).

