### Criteria Analysis

According to CONSORT 2010, interpreting a noninferiority trial’s results depends on where the CI for the treatment effect lies relative to the margin of noninferiority –∆NI and the null effect. The lower bound of the one-sided (1–α)×100% CI for the treatment effect must be above the margin –ΔNI to declare that noninferiority has been shown [45].

Once noninferiority is evident, it is acceptable to assess whether the new follow-up appears superior to the reference follow-up, using an appropriate test or CI, with a significance level defined a priori and with an intention-to-treat (ITT) and a per-protocol (PP) analysis. All randomized patients will be included in the ITT analysis, including children assessed at T1 or T2, after the time allowed by the protocol. The PP population will include only participants without major deviations. These patients must have completed at least 50% of the prescribed training time and at least 50% of the reading therapy sessions outlined in the protocol.

In this context, if the noninferiority is shown (based on both ITT and PP analyses), superiority will then be tested for the same primary end point, as described in the European Medicines Agency (EMA) guidelines [46]. Superiority will be tested using a *t* test at a 2-sided 5% significance level.

The type I error rate will be controlled using a hierarchical testing procedure for secondary end points. A subsequent end point will only be tested if the previous end point’s noninferiority test is statistically significant.

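### The primary variable is a 12-week word count in one section and a 12-week change in another; 90% power is shown only for change, and a baseline-adjusted analysis would settle it at no cost

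*Protocol article*

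**What the plan says.** All references are to the protocol article.

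- **Outcomes:** "The primary outcome of this study is reading accuracy, which will be measured by the number of correctly read words using the EVALEO" two-minute word reading test. On timing: "Noninferiority will be evaluated 12 weeks after the start of training with Poppins Clinical for the experimental group", or 12 weeks after baseline for controls. Table 1 gives the same measure. Neither place mentions change from T1.
- **Statistical Justification of the Sample Size, variable:** the trial is sized to show noninferiority "on the evolution of reading accuracy over 12 weeks". The hypotheses do not settle whether that means a T2 value or a change, because each parameter is defined only in the form "is the mean of the outcome in the experimental arm".
- **Same section, margin:** "they established that a difference of 5 words or fewer between groups would represent a clinically acceptable margin of noninferiority". The committee was informed by a mean 8-week progression of 7.7 words (SD 12.9) in the placebo group of the earlier trial.
- **Same section, SD:** "The SD of the outcome in each group was estimated at 12.7 words from the ML-01 study". The Discussion (Principal Findings) attaches 12.7 to that same 8-week progression.
- **Criteria Analysis:** noninferiority is declared when the lower confidence bound for the treatment effect lies above the margin. No estimator or model is named for that step. For the later step: "Superiority will be tested using a *t* test at a 2-sided 5% significance level".
- **Study Procedure:** a T1 evaluation precedes randomization, which is done "using blocks of size six to maintain a 1:1 ratio, with stratification based on" schooling level.

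**The concern.** A count at 12 weeks and a change over 12 weeks have the same expected between-arm difference under randomization, so a margin of 5 words can serve both. Their variances are not the same. The children are aged 7 to 11 and span CE1 to CM2, so raw counts may vary widely between children, and that spread largely cancels in a change score when T1 and T2 are well correlated. An SD taken from a progression then understates the SD of the count.

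Two things are at stake. First, whether 306 children are enough depends on which variable is analysed. Second, in a trial where families and therapists know the allocation, an open choice between count and change should be closed before anyone sees results by arm.

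In addition, the one test that is named uses neither the T1 score nor schooling level, although both are already available.

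**Working it through.** **Inputs from the article:** margin 5 words; SD 12.7; one-sided 2.5%; power 90%; 137 per arm; 10% dropout; 306 in total. A true difference of zero is assumed, the usual convention for noninferiority.

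**1. Reproduce the stated sample size.** Normal approximation: n = 2(1.960 + 1.282)² × (12.7/5)² = 2 × 10.51 × 6.452 = 135.6, so 136 per arm. The exact noncentral-t calculation for an unadjusted two-sample t test gives 137, as stated. Dropout: 137/0.9 = 152.2, so 153 per arm and 306 in total. The standardized margin is 5/12.7 = 0.39, also as stated.

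**2. Power if change is analysed.** With SD 12.7 and 137 per arm, the noncentrality is 5/(12.7 × √(2/137)) = 3.26 and power is 90.1%. With the SD of 12.9 given elsewhere in the same section, power is 89.2% and 141 per arm would be needed, a minor difference.

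**3. Power if the T2 count is analysed without adjustment.** The article gives neither the raw SD nor the T1–T2 correlation, so a range is assumed. Take 12.7 as the SD of change and the same raw SD, s, at T1 and T2. Then:

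- implied correlation: r = 1 − 12.7²/(2s²)
- ANCOVA residual SD: s√(1 − r²), which equals 12.7 × √((1 + r)/2) and so never exceeds 12.7

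Power at 137 per arm, margin 5, one-sided 2.5%:

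| Assumed raw SD | Implied r | t test on T2 count | t test on change | ANCOVA residual SD | ANCOVA on T1 |
|---|---|---|---|---|---|
| 12.7 | 0.50 | 90.1% | 90.1% | 11.00 | 96.3% |
| 15 | 0.64 | 78.5% | 90.1% | 11.51 | 94.8% |
| 20 | 0.80 | 54.1% | 90.1% | 12.04 | 92.8% |
| 25 | 0.87 | 37.8% | 90.1% | 12.28 | 91.9% |
| 30 | 0.91 | 27.9% | 90.1% | 12.41 | 91.3% |
| 40 | 0.95 | 17.6% | 90.1% | 12.54 | 90.8% |

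The unadjusted count loses power relative to change whenever r exceeds 0.5, that is, whenever s exceeds 12.7.

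**4. The other reading of 12.7.** Suppose 12.7 were the SD of the count, as a literal reading of the sample-size section together with Outcomes would have it. The t test on the count then has 90.1% power. The t test on change has 78.4% at r = 0.3, 90.1% at r = 0.5 and 98.7% at r = 0.7. ANCOVA has 92.6%, 96.3% and 99.5%. It therefore stays above 90% under either reading.

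**5. Why ANCOVA settles count versus change.** If T2 − T1 = a + b·arm + c·T1, then T2 = a + b·arm + (c + 1)·T1. The treatment coefficient b and its standard error are identical in the two models. Adding schooling level to both does not alter this.

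**The case against.** The strongest reply is that the article means change throughout. Outcomes names the construct, the instrument and the time of evaluation; it does not say that raw T2 counts will be compared. Table 1 gives no outcome as change or final value. The sample-size section, the basis of the margin and the SD all point to progression. On that reading the plan is coherent, its sample size reproduces, and only a reference to change from T1 is missing. This largely stands, and it limits the point to an inconsistency in how the variable is described.

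Three stronger readings might be inferred, and the documents do not support them:

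- **That the trial is underpowered.** The low figures apply only to an unadjusted T2 comparison, which the article never explicitly commits to, and they rest on assumed raw SDs. At a correlation of 0.5 there is no loss.
- **That ANCOVA is needed to reach 90% power.** The unadjusted t test on change already gives 90.1%. Over raw SDs of 15 to 40, ANCOVA adds roughly 1 to 5 percentage points.
- **That an unadjusted t test is the noninferiority analysis.** The t test is named for the conditional superiority step only. The model behind the noninferiority bound may be in an analysis plan that is not shown, and its absence from a journal article is not a fault.

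What remains is that the printed definition of the primary outcome and the printed basis of its power do not match, and that an unadjusted test is fixed for superiority on the primary end point.

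**Conclusion.** The point holds in limited form. The primary variable is a 12-week count in Outcomes and Table 1 and a 12-week evolution in the sample-size section. With 12.7 taken as the SD of a progression, as the Discussion presents it, 90% power at 137 per arm is supported for change (90.1%) but not for an unadjusted comparison of T2 counts if their SD exceeds 12.7. At assumed raw SDs of 15, 20 and 30, power would be about 79%, 54% and 28%.

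Those three figures assume equal SDs at T1 and T2 and a true difference of zero; the raw SD itself is an assumption. The direction is firmer than the size: it requires only a T1–T2 correlation above 0.5, which is plausible for the same reading test repeated after 12 weeks but is not documented. The further gain from adjusting for schooling level cannot be quantified from the article.

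This is a clarification with a free precision gain. It does not show that the planned sample size is wrong.

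**What to change.** State one primary estimate in Outcomes, Table 1, the sample-size section and Criteria Analysis: the between-arm difference in T2 EVAL2M correct words from an ANCOVA with the T1 EVAL2M score and schooling level (the stratification factor) as covariates. Compare its one-sided 97.5% lower bound with −5 in both the ITT and PP populations. Use the same model, at the two-sided 5% level, in place of the t test for superiority. In the sample-size section, say that 12.7 is the SD of change if that is what it is, and reconcile it with the 12.9 given for the same progression.

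The cost is wording only, in the protocol and the analysis plan, settled before unblinding. T1 scores and schooling level are already collected. No extra participants, visits or assessments are needed.

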### Statistical Justification of the Sample Size

The sample size determination was based on the primary end point, which is to demonstrate the noninferiority of a follow-up with reading therapy every 2 weeks, in addition to the use of the digital medical device (Poppins Clinical), compared with a follow-up with reading therapy every week, on the evolution of reading accuracy over 12 weeks. The null (H0) and alternative (H1) hypotheses for noninferiority trials may take the following form:

H0: experimental (EXPE) is inferior in terms of the mean response, μEXPE–μCONT≤−ΔNI.H1: experimental is noninferior in terms of the mean response, μEXPE−μCONT>−ΔNI.

Where μEXPE is the mean of the outcome in the experimental arm, and μCONT is the mean of the outcome in the control arm. The noninferiority limit, –ΔNI, is defined as the threshold at which the mean difference between the experimental arm and the control arm becomes clinically unacceptable.

The noninferiority margin was determined through a formal expert committee meeting, combining independent experts and investigators. The committee was structured to ensure both independence and relevant expertise. Two independent experts were selected for their complementary expertise: a neuropediatrician who pioneered diagnostic recommendations for learning disorders in France, and a speech therapist who codeveloped the standardized assessment tool used as the primary outcome in this study (EVALEO 6-15). The two investigators of the study, both professors in child psychiatry with extensive research experience in neurodevelopmental disorders, provided their methodological expertise. A fifth expert, a neuropsychologist with experience in written language rehabilitation guidelines and as a reviewer of good practice recommendations, was included as a scientific advisor. All experts were active clinicians and researchers in learning disabilities.

The committee’s decision was informed by empirical data from the previous randomized controlled trial (ML-01), showing a natural progression of 7.7 (SD 12.9) correctly read words over 8 weeks in the placebo group [26]. Based on these data and their collective clinical experience, they established that a difference of 5 words or fewer between groups would represent a clinically acceptable margin of noninferiority. This threshold was unanimously approved by the full committee after a structured discussion of potential age-related variations in reading progression.

The SD of the outcome in each group was estimated at 12.7 words from the ML-01 study [26]. The maximum acceptable inferiority for experimental versus control on the primary outcome is therefore expected to be a standardized difference (Cohen *d*=0.39), which corresponds to a label between small or medium, depending on the guidelines (R effect size package) [44].

Considering a one-sided significance level of 2.5% and a power of 90%, it is necessary to include 137 participants per group (G*Power 3.1). Assuming a 10% drop-out rate, the final estimate is 306 participants in total (or 153 participants per arm).

